### Dissemination

The results of the evaluation will be disseminated to the stakeholders, Aboriginal and Torres Strait Islander and non-Aboriginal and Torres Strait Islander community members and wider national and international research fraternity using a range of academic and non-academic dissemination channels, namely scientific journals, conferences, community talks, email newsletters and social media. Academic channels will include presentation of findings at academic conferences (local, national, and international) as well as publication in open access journals to facilitate greater access to researchers and stakeholders in resource poor settings. Non-academic dissemination will include circulation of an individualized progress report/newsletter to all participating services and organisations. If COVID-19 impact continues, all in-person presentations will be replaced by Zoom presentations at sites where travel restrictions are in place. Results will also be disseminated to the stakeholders and public via the iSISTAQUIT website and social media pages using engaging content to further improve user engagement with iSISTAQUIT. A policy report including recommendations will be written and disseminated to peak bodies and stakeholder organisations.

### Governance

The iSISTAQUIT project is governed by an academic panel comprising Aboriginal and Torres Strait Islander people, Indigenous people from other nations, and non-Indigenous people. A National Aboriginal and Torres Strait Islander Advisory Panel provides cultural oversight. A Social Media Panel provides guidance on the social media campaign; an educational panel guides the e-Learning modules and the medical practice software development. Membership of the panels is from peak organisations and health services and comprises at least 50% Aboriginal and Torres Strait Islander people. A recruitment and engagement framework is being co-developed with Aboriginal stakeholders and panel members to provide the cultural direction and a values base for the research and all its aspects. The recruitment and engagement framework describes how the iSISTAQUIT project is guided by peak bodies, Aboriginal health services and community members. Our belief is working together in common goals to support communities to live their healthiest life by quitting smoking. iSISTAQUIT values two-way shared learning and upskilling health care professionals for long term sustainability. Connection via referral pathways, promotion and partnerships is key. The co-developed engagement values are core to the project.

#### Status and timeline

The recruitment of sites has begun and to date 92 health providers have been enrolled and 42 health providers have completed training. Site recruitment will be completed by August 2022. All participating HCPs will complete training by October 2022. Data collection will be completed by November 2022. Data analysis and reporting of results will be completed by December 2022. The social media campaign was launched in December 2021 and evaluation completed by October 2022.

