#### Option 1. Evaluation research package

HCPs will be required to consent to completing the self-paced training modules, the reflective workbook and the pre- and post-training surveys (4 surveys in total). The training surveys will provide evidence on changes in knowledge, attitude and behaviours of the HCPs related to smoking cessation care. HCPs will be entered into a prize draw for completing all surveys and will have an option to claim CPD points.

The full iSISTAQUIT Evaluation-Research package consists, in addition to the training resources (treatment manual, patient flipchart and My Journey (patient) booklet), a) the provision of a carbon monoxide meter and oral nicotine replacement therapy (NRT), and, b) the choice of two medical practice software templates (Pen CS Topbar or Communicare) which aid and support the HCPs to enter the data about the patient’s medical consultation and the characteristics of the women’s quit attempts. The templates will be also utilised to guide the consultation according to the training using the ABCD approach [43]. ABCD approach stands for A—ask/assess; B—brief advice; C—cessation; and D—discuss the psychosocial context of smoking. This approach has been previously used in ICAN QUIT in Pregnancy and the SISTAQUIT RCT project.

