Implementation	1. HCP iSISTAQUIT usage rate	• Number of HCP who used the iSISTAQUIT/ABCD template to engage women in smoking cessation care over the first 3 months /Number of HCP that commenced the training (OM, PTA, CCI) • Analysis of number and type of BCTs used from the template	• Online through Moodle, HPMI at 3 months and 6 months
Maintenance	1. Descriptive statistics (number and percentage)	• HCP’s/services that ask for more iSISTAQUIT resources (treatment manuals, patient flip charts, my journey booklets). (OS, AU) • HCPs that report iSQ training is a current part of their normal work. (OS) • HCPs that report iSQ training will become part of their normal work at 3 months post training. (OS) • Ongoing/long term use of the iSISTAQUIT ABCD template. (PTA, CCI) • Services interested in offering iSISTAQUIT training and resources (if available) to new HCPs joining the service after project completion. (QA)	• Qualitative analysis/audit of qualitative interviews by an external Aboriginal service. • The 3-month HCP survey. • Pen CS Topbar or Communicare de-identified aggregated quarterly data will provide iSISTAQUIT/ABCD template utilisation data until end of current study completion (31 December 2022). • End of study interviews

HS: health services; HCP: health care professional; ABS: Australian Bureau of Statistics.

CPD: Continued professional development; HPMI: Hunter Postgraduate Medical Institute; NRT: Nicotine Replacement therapy; iSQ: iSISTAQUIT

CL: Communication Log

RF: Registration form

RACGP: Royal Australian College of General Practitioners

PTA: Pen CS Topbar application

SCC: Smoking Cessation Care.

CCI: Communicare iSISTAQUIT Clinical Item

OS: Online Survey

QA: Quantitative analysis

AU: Audit

OM: Online through Moodle

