#### Evaluation plan

iSISTAQUIT training: Evaluation will be done using the RE-AIM framework, which systematically evaluates the Reach, Effectiveness, Adoption, Implementation and Maintenance of implementation studies. For details see, Table 2.

Descriptive statistics will be used to present numbers, rates, proportions and trends in the data collected through surveys, Likert scales and service level data available through data collection tools described in Table 2. Thematic analysis will be used to analyse qualitative data collected during end of study interviews with practitioners, managers and research facilitators at the services.

Knowledge, attitudes and practices related to SCC: Differences in practitioner online survey responses from pre-training (referent period) to immediate post- and 3 months post-training will be assessed using linear mixed effects regression models, including fixed categorical effects for time, and a random intercept for site to model correlated responses for practitioners from the same service.

Social media campaign: The success of social media campaign will be assessed using surveys, qualitative methods, and social media metrics. More details are available from Table 3.

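### Data collection closes in November 2022, so health care professionals who finish training after about 31 August 2022 cannot give the 3-month survey, and October finishers lack a full 3-month template window

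*Protocol article*

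**What the plan says.** **Dates.** Under Status and timeline, the article states "All participating HCPs will complete training by October 2022. Data collection will be completed by November 2022". It adds "Data analysis and reporting of results will be completed by December 2022". Site recruitment stays open until August 2022.

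**Survey outcomes.** Under Evaluation plan, differences in practitioner responses from the pre-training period "to immediate post- and 3 months post-training will be assessed using linear mixed effects regression models". The Effectiveness rows of Table 2 use the same three survey times for barriers and enablers and for knowledge, attitudes and practices. The Maintenance row takes its normal-work reports from the 3-month survey.

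**Template outcomes.** The Implementation row of Table 2 defines a usage rate. The numerator is HCPs who used the template over the first three months, and the denominator is HCPs who commenced training. Its sources are Moodle and the two practice-software templates. The data-source cell reads "Online through Moodle, HPMI at 3 months and 6 months". The Maintenance row speaks of "template utilisation data until end of current study completion (31 December 2022", which is later than the November close.

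**Number of surveys.** The Option 1 section requires "pre- and post-training surveys (4 surveys in total" and gives no times for the four.

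**The concern.** The deadlines and the follow-up times sit in the same article and do not fit together. A person may finish training on a permitted date and have a 3-month survey due after collection, analysis and reporting have all closed. The article sets no earlier training cut-off for the 3-month analyses, exempts no late finishers and does not extend collection for them.

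The loss would follow the calendar. Because sites may join until August 2022, it is likely to include HCPs at the latest sites. The 3-month results would then describe earlier finishers without saying so. The exposed outcomes are 3-month practice change, barriers and enablers, the normal-work reports, and template use over the first three months. Practice change suffers most, because a survey taken immediately after training leaves little or no time for practice to change.

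**Working it through.** The plan gives no figure of its own on this point, so the check is date arithmetic.

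**Inputs**
- Last permitted training completion: October 2022, taken as 1 to 31 October (Status and timeline).
- Close of data collection: November 2022, read favourably as 30 November (Status and timeline).
- End of template data: 31 December 2022 (Table 2, Maintenance).
- Follow-up: 3 months (Table 2; Evaluation plan), with a 6-month data-source entry (Table 2, Implementation).

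**When the 3-month survey falls due** (completion date + 3 months)

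| Training finished | 3-month date | Days to 30 Nov 2022 | Days to 31 Dec 2022 |
|---|---|---|---|
| 31 Aug 2022 | 30 Nov 2022 | 91 | 122 |
| 1 Oct 2022 | 1 Jan 2023 | 60 | 91 |
| 31 Oct 2022 | 31 Jan 2023 | 30 | 61 |

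**Latest completion date that still fits** (closing date − follow-up)
- Survey, 3 months: 30 Nov 2022 − 3 months = about 30 to 31 August 2022. If collection closed on 1 November, this would be 1 August.
- Template, 3 months: 31 Dec 2022 − 3 months = about 30 September 2022.
- A 6-month Moodle record: 30 Nov 2022 − 6 months = about 30 to 31 May 2022.

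These limits assume a response on the due date, with no allowance for late replies.

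**Effect on the usage rate.** Suppose the three months start at training completion. An October finisher is then observed for 61 to 91 days. First use after 31 December but within three months is not counted, yet the person stays in the denominator. Truncation can therefore lower the rate or leave it unchanged; it cannot raise it. A 1 October finisher is only one day short, and a 31 October finisher is 31 days short.

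**Closing the window.** Keeping the October training deadline requires 3-month collection to run to 31 January 2023.

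**November against 31 December.** Template data that run to 31 December lie outside a collection period that ends in November. They also cannot be fully analysed and reported by December.

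**The case against.** The strongest reply is that these are outer limits in a status paragraph. Most HCPs may finish well before October. Training takes about four hours, so even a site that joins in August could finish quickly. The immediate post-training contrast, reach and training-completion rates are unaffected. The mixed model keeps people who have no 3-month record. All of this stands, and it limits the size of the problem. It does not remove the conflict: the model cannot create 3-month data for late finishers, and its 3-month estimate must then assume that they resemble earlier ones.

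Four stronger readings are tempting, and the article does not support them.

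- **A stated loss of power.** A paired approximation, Φ(0.2/√(2(1−r)/n) − 1.96), gives 90% at n = 20 × 8 = 160 if r is about 0.695. It gives 80% at n = 120 and 63% at n = 80. The article states no such correlation (at r = 0.5, power is already 72% with n = 160), and the shares lost are assumptions. The sample-size section powers a pre-to-post comparison without naming three months, and the planned model is not a paired test.
- **A count of those affected.** The 42 completions among 92 enrolled are undated and are not said to be Option 1 only, so setting them against 160 may mix populations.
- **Maintenance biased downward.** The normal-work items are survey reports with no stated denominator. Among respondents, missing late finishers cost precision, and the direction of any bias is unknown.
- **Lost 6-month outcomes.** Six months appears once, in a data-source cell, and no outcome is defined there. The four surveys do not prove a 6-month wave, since the Implementation readiness section adds a post-training survey of its own.

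**Conclusion.** The concern holds in limited form. On the stated dates, no HCP who finishes training after about 31 August 2022 can supply the 3-month survey before collection closes. October finishers also lack a full 3-month template window, even with the later 31 December date.

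The survey conclusion rests only on the article's dates, with 30 November as the favourable reading of the close. The usage conclusion also assumes that the three months run from training completion. The article does not define the start, and the truncation would be smaller if they ran from commencement.

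The number of HCPs affected cannot be computed from the article, and no loss of power should be attached to the point. It is still worth correcting before the data close, because neither the model nor a later analysis plan can recover a survey that was never collected.

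**What to change.** **Preferred.** Keep the existing 3-month survey link and the template extract open to 31 January 2023, and run the 3-month analyses after that date. The cost is about two more months of an online survey already built, one more month of template extract, and reporting that slips past the stated December 2022 completion.

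**If the close cannot move.** State that 3-month survey results cover only HCPs trained by about 31 August 2022. Compute the 3-month usage rate only among HCPs with a full template window, which means trained by about 30 September 2022 with the 31 December extract. The cost is that the latest sites are under-represented, because the survey cut-off coincides with the close of site recruitment. The report should say so.

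**Either way.**
- State the date from which the three months of template use are counted.
- Reconcile the November and 31 December 2022 end dates.
- Remove the 6-month entry in the Implementation row of Table 2, or limit it to HCPs trained by about 31 May 2022.

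These are wording changes only.

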## Conclusion

Smoking in pregnancy is a very high priority for Aboriginal and Torres Strait Islander peoples nationwide. Although numerous community-led and local initiatives are underway within many Aboriginal communities in Australia, there is no effective national smoking cessation program for Aboriginal women. iSISTAQUIT program would facilitate rapid translation of research into practice.

This innovative research, using a multi-component intervention, aims to practically apply and integrate what is already known into a highly translatable approach in real-world primary care settings into AMS and Mainstream services. The results from this study will develop new knowledge about digitally delivered smoking cessation training for health professionals who care for pregnant Aboriginal and Torres Strait Islander women. The results from this study will also inform the GACD/NHMRC funded iSISTAQUIT scale-up project (reference: GNT2009206).
